#### Outcome Definitions and Measures

Outcomes were informed by a large primary care trial on improving prevention and management of chronic conditions in primary care [51], a quality index created for primary care with items measurable in EMRs [52], and consideration of data capture across the networks of CPCSSN. We further conceptualized outcomes according to whether they represent aspects of access, comprehensiveness, or appropriateness (Table 1).

**Table 1 table1:** Outcomes and outcome measures.

Population		Indicator		Related domain		Data source^a^
**Number and types of encounters**						Encounter, encounter diagnosis, and billing
	All patients in our defined cohort	Overall number of all encounters	Access			
	Patients with the CPCSSN^b^ case definition of diabetes and HF^c^	Overall number and types of diabetes-related and HF-related investigations	Comprehensiveness			
**Diagnoses addressed in encounters**				Comprehensiveness and appropriateness		Encounter, encounter diagnosis, and billing
	All patients	Number of different diagnoses addressed per patient per year				
	Patients with ≥1 condition with the validated CPCSSN case definition	Number and proportion of chronic conditions (ie, CPCSSN case definitions) addressed by physician at least once a year				
	Patients with the CPCSSN case definition of diabetes and HF	Overall number and types of diabetes-related and HF-related investigations				
	Patients with the CPCSSN case definition of diabetes and HF	Proportion of patients with diabetes-related encounter and HF-related encounter every 6 and 12 months (as appropriate for condition)				
**Services provided**				Comprehensiveness		Billing, vaccine, and medication
	Patients age ≥65 years	Number of patients receiving pneumococcal vaccine and influenza vaccine				
	Patients with the CPCSSN case definition of diabetes and HF	Proportion of patients with influenza vaccination				
**Procedures performed**				Appropriateness		Billing
	Patients with the CPCSSN case definition of diabetes	Proportion of patients with foot examinations in last 12 months				
**Physical examinations**				Appropriateness		Examinations
	All patients in our defined cohort; all patients grouped by CPCSSN case definition	Proportion with BP^d^ measured every 6 months or every 12 months (as appropriate for condition)				
**Referrals made to specialists**				Comprehensiveness		Referral
	All patients in our defined cohort; all patients grouped by CPCSSN case definition	Overall number and types of referrals; proportion referred to cardiology, endocrinology (as appropriate for condition)				
**Investigations performed**				Appropriateness		Laboratory
	All patients in our defined cohort	Number of vitamin D, CBC^e^, eGFR^f^, ACR^g^, and liver function tests performed				
	Patients with CKD^h^	Number with and frequency of eGFR and ACR tests				
	Patients without diabetes	Number with HbA_1c_^i^, FBS^j^ measured (screening)				
	Patients taking or not taking statins	Number with and frequency of lipid panel/LDL^k^				
	Patients taking or not taking levothyroxine	Number with and frequency of TSH^l^ measured				
	Patients with the CPCSSN case definition of diabetes	Proportion with HbA_1c_ measured every 6 months and every 12 months				
**Monitoring results**				Appropriateness		Examination
	All patients in our defined cohort; all patients grouped by CPCSSN case definition and age	Proportion with BP ≤140/90 or ≤130/80 (as appropriate based on chronic conditions and age); proportion of patients in the following sBP^m^ ranges: ≤130, 131-140, 141-150, 151-160, and >160				
**Medications**				Comprehensiveness and appropriateness		Medication and risk factor
	Patients with the CPCSSN case definition of diabetes	Proportion of patients with and overall number and frequency of metformin prescriptions, insulin prescriptions, and other oral antidiabetic prescriptions^n^				
	Patients with the CPCSSN case definition of HF	Proportion of patients with and overall number and frequency of β-blocker prescriptions, ARB^o^ prescriptions, and ACE-I^p^ prescriptions				
	Patients who smoke	Number of patients with NRT^q^ prescription				

^a^CPCSSN data table.

^b^CPCSSN: Canadian Primary Care Sentinel Surveillance Network.

^c^HF: heart failure.

^d^BP: blood pressure.

^e^CBC: complete blood count.

^f^eGFR: estimated glomerular filtration rate.

^g^ACR: albumin-to-creatinine ratio.

^h^CKD: chronic kidney disease.

^i^HbA_1c_: hemoglobin A_1c_.

^j^FBS: fasting blood sugar.

^k^LDL: low-density lipoprotein.

^l^TSH: thyroid-stimulating hormone.

^m^sBP: systolic blood pressure.

^n^Other oral antidiabetic medications include classes such as sodium-glucose cotransporter-2 inhibitors, sulfonylureas, meglitinides, dipeptidyl peptidase 4 inhibitors, etc.

^o^ARB: angiotensin receptor blocker.

^p^ACE-I: angiotensin-converting enzyme inhibitor.

^q^NRT: nicotine replacement therapy.

*Access* to the practice will be measured as the overall number of encounters.

*Comprehensiveness* refers to primary care addressing “all problems in the population (with short-term referral as needed), except those that are too unusual (generally a frequency of less than 1 or 2 per thousand in the population served) for the primary care practitioner or team to treat competently” [1]. As indicators of comprehensiveness, we will measure number of different diagnoses addressed per patient per year, proportion of patients’ chronic conditions addressed at least once a year, number of pneumococcal vaccines and influenza vaccines in patients 65 years or older, and number of prescriptions for nicotine replacement therapy

*Appropriateness* will be examined in 2 ways: laboratory tests that are indicated for monitoring of chronic conditions but may be ordered more frequently than necessary (eg, hemoglobin A_1c_ in diabetics) and laboratory tests that are frequently ordered routinely (or for screening purposes) but may be overused in certain populations, including thyroid function tests, vitamin D, albumin-to-creatinine ratio, and lipid panel testing [53]. We hypothesize that some of these tests, while indicated at a base frequency, may be commonly overused; thus, their frequency may have declined during the pandemic.

Diabetes and heart failure are 2 chronic conditions where aspects of care can be reasonably evaluated in CPCSSN. We will describe care across the population in terms of frequency of contacts, laboratory tests and investigations, and medications prescribed that would suggest care that is in step with evidence-based recommendations [54]. For patients with diabetes, we will measure the percentage of patients with a diabetes-related encounter every 6 and 12 months; percent with a foot examination in the last 12 months; percent with a blood pressure measure and hemoglobin A_1c_ test every 6 and 12 months (and results); percent with influenza vaccination; overall number of diabetes-related investigations; percent referred to endocrinology; percent receiving, and number and frequency of metformin, insulin, and other antidiabetic prescriptions. For patients with heart failure, we will measure percentage of patients with heart failure–related encounters every 6 and 12 months; number of investigations (echocardiogram and blood tests); percent with a blood pressure measure every 6 and 12 months (and results); percent with influenza vaccination; percent receiving β-blocker, angiotensin-converting enzyme inhibitors, and angiotensin receptor blockers; and percent referred to cardiology and other specialists.

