## Introduction

The presence of strong primary care systems has been shown to be associated with superior and more equitable health outcomes in the population [1-6]. Core elements of primary care that contribute to population health outcomes include access, continuity, comprehensiveness, coordination, person focus, and equity enhancement [7]. Chronic diseases are common and represent the leading causes of death worldwide [8]. The core elements of primary care make this setting ideal for managing chronic diseases [4,9], and family medicine and other primary care services provide the majority of care for chronic diseases across the lifespan [4,10]. With increasing age, there is an increasing prevalence of multiple chronic diseases [11], and these patients require careful management to reduce morbidity and mortality and improve quality of life [12]. Life-limiting chronic diseases such as chronic obstructive pulmonary disease, heart failure, and chronic kidney disease [13-15] affect millions of people in Canada and are mostly managed in primary care [16-19]. Other conditions that are risk factors for numerous cardiovascular and cerebrovascular diseases (eg, diabetes and hypertension) are associated with poor health outcomes, and these are also managed in primary care [20].

On March 11, 2020, the World Health Organization declared the circulating SARS-CoV-2 as a pandemic. The SARS-CoV-2 pandemic placed a substantial strain on health care services for care of both COVID-19 illness (the majority of which was provided in primary care without need for hospitalization) and non–COVID-19 illness [8,21]. The documented early impacts of the COVID-19 pandemic were reductions in the number of patients visiting primary care offices [22], dramatic increases in remote care especially for older patients [22,23], and new strategies to maintain care such as implementing wellness checks for high-risk patients [24,25].

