### Variables of Interest

#### Primary Exposure

The primary exposure is the start of the pandemic in March 13, 2020. This date was selected as it marks the beginning of Canadian provincial governments responding to the formal declaration of the pandemic by the World Health Organization on March 11, 2020, by enforcing sweeping public health and safety measures. The prepandemic time frame used is defined as June 22, 2018, through March 12, 2020. The pandemic time frame used in this study runs from March 13, 2020, through December 31, 2022. In addition to comparison between these 2 periods, 30-day interval rates will also be calculated for selected outcomes and indicators where possible.

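### The yearly count of distinct diagnoses can include COVID-19 essentially only in the pandemic window, so its pre-post change carries an upward component that can hide a loss of other diagnoses

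*Protocol article*

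**What the plan says.** In the protocol article, Outcome Definitions and Measures, Table 1 (block on diagnoses addressed), the first indicator is "Number of different diagnoses addressed per patient per year". It applies to all patients and draws on the encounter, encounter diagnosis and billing tables. The text after the table gives it a purpose: "As indicators of comprehensiveness, we will measure number of different diagnoses addressed per patient per year". The concept itself "refers to primary care addressing “all problems in the population (with short-term referral as needed), except those that are too unusual" for the practice to treat competently.

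Primary Exposure fixes the two sides of the comparison: "The prepandemic time frame used is defined as June 22, 2018, through March 12, 2020", and "The pandemic time frame used in this study runs from March 13, 2020, through December 31, 2022". The Introduction describes the strain on services as "care of both COVID-19 illness (the majority of which was provided in primary care without need for hospitalization) and non–COVID-19 illness", so it names COVID-19 as primary care workload and sets it apart from other illness.

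Analyses of Changes Over Time plans paired pre-post tests, then regression adjusting for age, sex, comorbidity count, neighbourhood income quintile and CPCSSN network. Nowhere does the article separate COVID-19 codes from the rest of the diagnosis count.

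**The concern.** The indicator counts categories of diagnosis, not visits. One category can be recorded in essentially only one of the two windows. A patient with a single COVID-19 code in a pandemic year can gain one distinct diagnosis that could not have been gained before March 2020. In a within-patient comparison that gain goes straight into the estimated change. The planned covariates cannot remove it, because it is tied to the period itself.

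The article reads this indicator as a signal. Key Findings lists a change in diagnoses addressed among the possible signs of gaps in care, and the closing Conclusions say the study will either point out gaps or reassure. If practices dealt with fewer of their patients' other problems while adding COVID-19, the combined count could show a smaller fall, no change or a rise, and the reassurance would be misplaced.

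**Working it through.** **The plan's own figures.** The article gives no expected value for this indicator. Its only sample sizes are 1276 and 1432 pairs, for a binary outcome moving from 50% to 55%. They reproduce with a paired-proportions formula, assuming two-sided 5% and 80% power. The discordance is 0.4005 (correlation 0.2) or 0.4503 (correlation 0.1), giving n = 1255.0 and 1411.2. Adding 1/0.05 = 20 gives 1275.03 and 1431.2, rounded up to 1276 and 1432. They do not bear on a count of diagnoses.

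**Windows (Primary Exposure).** June 22, 2018 to March 12, 2020 is 630 days, with essentially no opportunity for a COVID-19 code. March 13, 2020 to December 31, 2022 is 1,024 days (659 if data end in December 2021), with opportunity throughout. This shows when the category is available, not how often it is used.

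**Notation.**
- m = prepandemic mean of distinct diagnoses per patient-year (not in the article; assumed 2 to 5).
- c = share of patients per year for whom a COVID-19 code adds a distinct diagnosis (not in the article; assumed 0.02 to 0.20). COVID-19 is treated as one category.
- L = proportional loss of all other diagnoses.

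**Formulas.** Change without COVID-19 = −L × m. Change with COVID-19 = c − L × m. The difference is +c and is never negative. The combined change is zero at L = c/m, so a loss up to c/m is fully hidden and a larger one is understated by c.

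**Loss fully hidden (c/m).**

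| c | m = 2 | m = 3 | m = 5 |
|---|---|---|---|
| 0.02 | 1.0% | 0.7% | 0.4% |
| 0.10 | 5.0% | 3.3% | 2.0% |
| 0.20 | 10.0% | 6.7% | 4.0% |

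**Measured change at m = 3.**

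| True loss of other diagnoses | c = 0.05 | c = 0.10 | c = 0.20 |
|---|---|---|---|
| 5% (−0.15) | −0.10 | −0.05 | +0.05 |
| 10% (−0.30) | −0.25 | −0.20 | −0.10 |

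Five of these six cells still show a fall. All six understate it, and one reverses the sign.

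**Against the precision of the study.** Study Timeline gives 875,934 patients. With an assumed SD of paired differences of 2 to 4, and treating patients as independent, SE = 2/√875,934 = 0.0021 to 4/√875,934 = 0.0043. The change detectable with 80% power is (1.96 + 0.84) × SE = 0.006 to 0.012. Even c = 0.02 exceeds this. If nothing else changed, the COVID-19 category alone would give a statistically significant increase. Clustering within practices would widen the SE.

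**Substitution.** Let s be the share of patients whose COVID-19 code took the place of another code, such as one for a respiratory infection. The version with COVID-19 still shows c − L × m. The version without it shows −L × m − s. The true change, −L × m, lies between them.

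**The case against.** The strongest reply is that COVID-19 belongs in the count. The article defines comprehensiveness by reference to all but the rarest problems in the population, and a practice treating COVID-19 is treating such a problem. This stands: the inclusive count is a legitimate measure, and the article is not wrong to define it. But it answers whether practices dealt with more or fewer kinds of problem in total, not whether they went on dealing with the others. Only the second speaks to gaps in care.

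Second, the article is condensed, and diagnosis groupings and code lists may sit in a fuller plan. This also stands, so the absence of a code list is not the point. The point is that the indicator as defined draws on different sets of possible diagnoses in the two periods.

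Third, much of the masking risk is covered elsewhere. The next row of Table 1 is confined to validated CPCSSN chronic conditions, which COVID-19 does not enter, and the diabetes and heart failure indicators are likewise untouched. A loss of chronic care would show there. What remains exposed is the loss of other diagnoses, and patients with no validated condition. Statistical Analysis and Power puts adults with at least one chronic condition at 65% of the 2018 database, which leaves about 35% without.

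Fourth, the sizes are assumed. That is true. The sign of the component follows from the definition and its magnitude does not; at c = 0.02 the hidden loss is only 0.4% to 1.0%.

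Fifth, simply dropping COVID-19 codes can err the other way where they replaced other respiratory codes. This stands, and it is why the fix asks for both versions. Key Findings also urges caution before firm conclusions, but caution cannot recover a component that is not reported separately.

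**Conclusion.** The point holds as a matter of comparability. The pre-post change in this one indicator contains an upward component equal to c, which neither the paired design nor the planned adjustment removes. Under assumed means of 2 to 5 and shares of 2% to 20%, it would fully hide a loss of other diagnoses of about 0.4% to 10% and understate a larger one. Neither input is in the article.

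A reader might infer that the indicator must rise during the pandemic. The article does not support that. Only the COVID-19 component is pushed up. The Introduction reports fewer chronic-condition visits early in the pandemic, and the total falls whenever L × m exceeds c. A reader might also extend the concern to comprehensiveness as a whole, which is not supported either, because the chronic-condition, diabetes and heart failure indicators are unaffected. This is a worthwhile and cheap improvement to one indicator, not a fault in the study as a whole.

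**What to change.** Report the pre-post change in distinct diagnoses per patient-year twice, with and without COVID-19 diagnosis codes, and give the share of patients with such a code in each year. Base any statement that other diagnoses were lost or maintained on the version without them. State in the code list whether COVID-19 exposure, testing or vaccination codes found in the encounter diagnosis or billing tables count as diagnoses.

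Read the two versions as an approximate bracket. Where COVID-19 codes replaced other respiratory codes, the version without them is biased slightly downward. COVID-19 contacts filed under non-specific respiratory codes stay in both versions and can push both up.

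The cost is a code list, one more run of the same analysis and one descriptive line, with no new data. Study Timeline says that only exploratory analyses had begun in May 2023, so at that stage the definition could still be settled before the main results.

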**Methods:**

This is a retrospective, single-arm, pre-post study using Canadian Primary Care Sentinel Surveillance Network (CPCSSN) data. CPCSSN is a research network supported by a primary care electronic medical record database, comprising over 1500 physicians and nearly 2 million patients. We are examining changes in care (eg, frequency of contacts, laboratory tests and investigations, referrals, medications prescribed, etc) among adults. We will also examine indicators specific to evidence-based recommendations for care in patients with diabetes and those with heart failure. We will compare rates of outcomes during key periods of the pandemic between March 13, 2020, and December 31, 2022, with equal time periods before the pandemic. Differences will be examined among specific subgroups of adults, including by decade of age, number of comorbidities, and socioeconomic status. Regression models appropriate to outcome distributions will be used to estimate changes, adjusting for potential confounders. This analysis is part of a mixed-methods study with a qualitative component investigating how patients with diabetes with or without concurrent heart failure perceived the impact of the pandemic on access to primary care and health care–related decisions. This study was approved by the Hamilton Integrated Research Ethics Board (14782-C).

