### Study Design

This protocol was designed using the RECORD (REporting of studies Conducted using Observational Routinely collected Data) statement [46]. We will conduct a retrospective closed cohort study with a single group using a pre-post design. We will examine prevention and management activities for exemplar conditions on the basis of having a validated CPCSSN case definition [47,48] (ie, diabetes and heart failure), having substantial prevalence in primary care, and either having high morbidity or being risk factors for morbidity if not well managed. Patient-level data extracted from the CPCSSN repository between 2018 and 2022 will be used to investigate changes in rates of presentation and clinical management of various chronic diseases before, and through the phases of, the pandemic.

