### Study Population

The study population is all patients who were 18 years and older in 2018, and some analyses will focus on subgroups of patients with specific chronic conditions. We will use the 2-year contact population as recommended previously for defining practice populations for primary care [49]. This method uses contacts within encounter, medication, and billing-related data tables, and has been used previously with CPCSSN data to produce national chronic disease estimates [50]. This method will be used in the period from March 13, 2018, to March 13 2020. We will use this population rather than the full CPCSSN patient population data (dating back more than 2 decades for some networks) to limit the size of the data set, while maintaining the patient population that is likely to have a relationship with a primary care practice during the study period. Although this approach may exclude patients who are younger, healthier, and less likely to seek primary care compared with patients with chronic conditions, we do not expect this to have a major impact on findings because this study focuses on the age group where chronic condition prevalence begins to increase and where screening guidelines apply (eg, diabetes). Therefore, this age group is more likely to see a primary care physician regularly.

People who died during the study period will be included up to the point of death using the death date if captured or the presence of a deceased status with date estimated from the most recent contact in CPCSSN data. Patients who were older than 105 years at the start of the COVID-19 pandemic will be excluded as a possible data error.

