### Future Analyses

We will attempt to extend our analyses to include the first half of 2022 when data become available if our timelines and resources allow. At the time of writing this protocol (May 2023), data were available up to December 2021. The additional 2022 data will allow us to investigate changes in primary care in the later portion of the COVID-19 pandemic, capturing the Omicron wave, and measure whether any changes identified in the earlier portion of the pandemic were sustained or returned to prepandemic patterns of care.

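### The pneumococcal vaccine count has no still-due denominator, so depletion and ageing into the 65+ group can move it with no pandemic effect

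*Protocol article*

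**What the plan says.** The article's Study Design section states: "We will conduct a retrospective closed cohort study with a single group using a pre-post design". Under Study Population, the group that is closed is adults, not older adults: "The study population is all patients who were 18 years and older in 2018".

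In Table 1, under services provided, the indicator for patients aged 65 or more is "Number of patients receiving pneumococcal vaccine and influenza vaccine". The text below the table lists, among the measures of comprehensiveness, "number of pneumococcal vaccines and influenza vaccines in patients 65 years or older". The table thus counts patients and the text counts vaccines. Both give a number, and both treat the two vaccines alike. The next row of Table 1 uses a proportion for influenza vaccination in diabetes and heart failure.

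On the windows, Primary Exposure says "The prepandemic time frame used is defined as June 22, 2018, through March 12, 2020" and "The pandemic time frame used in this study runs from March 13, 2020, through December 31, 2022". The abstract says instead that pandemic periods will be compared "with equal time periods before the pandemic". Future Analyses adds that, at the time of writing, "data were available up to December 2021".

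Analyses of Changes Over Time assigns the McNemar test to binary pre-post outcomes. Its adjustment variables are age below or above 70, sex, comorbidity count, income quintile and network. Earlier vaccination is not among them.

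**The concern.** A service that recurs, such as a seasonal vaccine, can be counted in two successive windows in the same people because everyone becomes due again. A service that most people receive once in the period cannot. Each patient who receives it in the first window leaves the pool of those due but remains in the group being counted.

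In the paired table, the cell for patients vaccinated in both windows is then close to empty. Nearly everyone vaccinated before the pandemic becomes a discordant pair of the yes-then-no kind. McNemar's test compares them with first-time vaccinations drawn from the remaining pool. The result mixes depletion, window length, ageing into the stratum and any real change in practice, and the listed covariates do not separate these.

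At stake is one comprehensiveness indicator. A fall could be read as a gap in care that is not there. With a longer second window or an inflow of new 65-year-olds, a stable or rising number could hide a real gap.

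**Working it through.** The plan gives no figure for this indicator, so there is none to reproduce. Its sample sizes (1276 and 1432) concern a change from 50% to 55% and are not affected.

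**Inputs from the article.** June 22, 2018 to March 12, 2020 is 630 days, or 630/365.25 = 1.725 years. March 13, 2020 to December 31, 2022 is 1024 days, or 2.804 years. To December 31, 2021 it is 659 days, or 1.804 years. The total span is (630 + 1024)/365.25 = 4.53 years.

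**Assumptions, not in the documents.** At most one dose per person in the span; a constant yearly probability h of vaccination while due, with h = 5%, 10% or 20%; no pandemic effect; no deaths.

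**Case 1: 65+ group fixed at the start.** Write q = 1 − h, T1 = 1.725, and T2 for the second window.

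- Share of the initially due vaccinated in window 1: A = 1 − q^T1
- Share vaccinated in window 2: B = q^T1 × (1 − q^T2)
- Count ratio = B/A; rate ratio per unit time = (B/A) × (T1/T2)

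For h = 10% and the stated windows: q^1.725 = 0.834, so A = 0.166. q^2.804 = 0.744, so B = 0.834 × 0.256 = 0.213. The count ratio is 1.28 and the rate ratio is 1.28 × 630/1024 = 0.79.

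| h | Count ratio, equal windows (630/630) | Count ratio, data to Dec 2021 (630/659) | Count ratio, stated (630/1024) | Rate ratio, stated (630/1024) |
|---|---|---|---|---|
| 5% | 0.915 | 0.956 | 1.45 | 0.89 |
| 10% | 0.834 | 0.869 | 1.28 | 0.79 |
| 20% | 0.681 | 0.706 | 0.99 | 0.61 |

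Under the stated windows the count ratio crosses 1 at a continuous uptake rate of about 0.219 per year, which is a yearly probability of 1 − e^(−0.219) = 0.197. With data to December 2021 it crosses 1 at about 0.026 per year.

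**What the paired test sees.** Suppose 10,000 patients are due at the start (an assumed number), with h = 10% and equal windows. Window 1 has 1662 doses and window 2 has 0.834 × 1662 = 1386, all discordant. McNemar's z = (1662 − 1386)/√(1662 + 1386) = 276/55.2 = 5.0, with no pandemic effect.

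**Case 2: age 65 attained over time.** Let u be the unvaccinated share of the 65+ group at the start, r the yearly inflow of unvaccinated new 65-year-olds as a share of that group, and h now a continuous yearly rate. The count between times a and b is r(b − a) + (u − r/h)(e^(−ha) − e^(−hb)). Assume u = 30% to 50%, r = 4% to 6% and h = 0.05 to 0.40. For two windows of 1.725 years:

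- Lowest ratio (u = 0.5, r = 0.04, h = 0.40): 0.169/0.268 = 0.63
- Level (u = 0.3, r = 0.06, h = 0.20): u = r/h, so the ratio is 1.00
- Highest ratio (u = 0.3, r = 0.06, h = 0.05): 0.0353/0.0291 = 1.21

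**Check of the remedy.** In Case 1, dividing doses by person-time while still due gives (1 − q^T)/[(1 − q^T)/(−ln q)] = −ln q. This is the same in both windows whatever their length; at h = 10% it is 0.105 per person-year. The artefact disappears under these assumptions.

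**The case against.** **The count need not fall.** A reader might infer that this number must drop through depletion and imitate a pandemic decline. The documents do not support that. Under the dates in Primary Exposure the raw count rises at 5% and 10% uptake and is almost level at 20%. The closed group is adults, so unless age 65 is fixed at a baseline date, people turning 65 refill the pool. This objection stands and limits the point to a bias of unknown direction.

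**The premise is external.** The article does not say how often pneumococcal vaccine is given. That is right, so the premise is carried as an assumption. The mechanism needs only that a dose makes a further one unlikely within about 4.5 years. The uptake, inflow and coverage values are also assumed.

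**An article condenses the plan.** The reference date for age 65 and eligibility rules may be set elsewhere, and Analyses of Changes Over Time promises proportions for each period. The first part is fair. But the measure itself is stated, twice, as a number. Dividing by a fixed 65+ group would also leave every count ratio in the table unchanged, because the denominator cancels.

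**Other safeguards.** The 30-day rates in Primary Exposure could help tell gradual depletion from an abrupt break in March 2020, and Key Findings urges caution before firm conclusions. The 30-day rates are promised only for selected outcomes, and caution does not remove a bias. Both soften the consequence.

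**Weight.** Pneumococcal vaccine is half of one of the four comprehensiveness items in the text, and Table 1 assigns further indicators to that domain. This stands.

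**Conclusion.** The point holds as a design weakness in one indicator. As written, the pneumococcal number can change between periods with no change in practice, and the paired comparison cannot separate this from a pandemic effect.

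With a fixed 65+ group and 5% to 20% yearly uptake, the spurious count ratio is 0.92 to 0.68 for equal windows and 1.45 to 0.99 for the stated windows, where the rate per unit time falls to 0.89 to 0.61. With ageing into the stratum and equal windows, the wider assumed ranges give 0.63 to 1.21. These figures illustrate scale and are not estimates for this cohort. They rest on one dose per person in the span, constant uptake among those due, and no deaths.

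It does not follow that the study will report a false decline, nor that influenza vaccination shares the problem if it is repeated each season. The sample size and the other indicators are untouched.

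**What to change.** Split the Table 1 row and the matching sentence on comprehensiveness.

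- **Pneumococcal vaccine.** In each period, report the rate per person-year among patients who are 65 or older when that period starts and have no earlier pneumococcal vaccine in the CPCSSN vaccine, billing or medication tables. Stop a patient's person-time at the dose, at death or at the end of the period. Compare the two as period-specific rates, not as a paired count. Person-time also deals with unequal windows.
- **Influenza vaccine.** Report it as a proportion per season.

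The cost is a wording change and one derived still-due flag. The downsides are small. Doses given outside the practice are missed, so some vaccinated patients stay in the denominator, and this indicator is no longer paired. The remaining pool may also consist of patients less inclined to be vaccinated, which a still-due rate does not correct. Including this indicator among the 30-day rates would help show whether any change coincides with March 2020.
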